### Outcome measures

Outcome measures will be recorded by an assessor blinded to group allocation. The primary outcome is *function (disability) *assessed by the Roland Morris Disability Questionnaire (RMQ) [34-36], a self-administered questionnaire with score 0-24, with 0 corresponding to no disability. The RMQ is a frequently used outcome measure in trials related to LBP.

The secondary outcomes are as follows:

• *Pain; *measured on a numerical rating scale from 0 to 10

• *Return to work; *reported as number of days from first visit to the health care provider until complete or partial return to work - and as a total number of days absent from work the following year

• *Overall satisfaction*; measured on a numerical rating scale from 0 to 10

• *Health related quality of life*; assessed by the EuroQoL-5D [37] and Patient-Generated Index (PGI) [38]

• *A cost-effectiveness analysis *will be carried out by using both the return-to work outcome and the EuroQoL 5D, and by estimating the total cost of all the four groups of doctors and physiotherapists in this trial.

### Compliance

In order to assess compliance with the treatment intervention, three initiatives are taken: Firstly, the intervention clinicians filled in a knowledge test before and after the 2-day seminar with [name]. This test has been developed by [name] and [name], and is frequently used when providing the "explain pain" courses. The test will be used again in one of the follow-up meetings throughout the project period.

Secondly, in order to evaluate the clinician's perception of the intervention he/she has provided, the clinicians reply to some questions regarding the content of the provided intervention for each of the patients included.

Thirdly, in order to evaluate the patient's perception of the intervention he/she has received, a telephone interview after the last treatment session is carried out. All included patients (regardless of group allocation) are asked identical questions.

### Data analysis

A daily checking for accuracy and completion of data forms and double data entry will be used to ensure quality of the data. Data will be analysed by a statistician who is blinded to group status. The primary analyses will be by intention-to-treat and we will restrict the number of analyses in order to reduce the possibility of Type I errors. For primary outcomes, a p value of < 0.05 will be considered statistically significant. For the secondary outcomes a p value of < 0.01 will be considered statistically significant.

Differences between the groups will be presented as a mean with 95% CI or in categories with odds ratio for categorical data. For the primary outcome of days to return to work a survival curves analysis with a log-rank statistic will be used to assess differences between the groups, and Cox's regression to assess the effects of treatment (group) status on hazard rates for time to return to work. A mixed model with group as a fixed factor will be used for the other outcome measures. If there is a significant difference between treatment groups, post-hoc analyses will be conducted. We will also test for potential confounding factors in these models. Analyses of prognostic factors will be carried out by multivariate regression models.

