### Sample size

The primary outcome of the study is patient-reported function as measured on a continuous measure (Roland- Morris Questionnaire). Based on previous Norwegian studies using the RMQ for patients with LBP, a clinically relevant difference between two groups can be estimated to be approximately 2 points with a SD of 3. This is also similar to a previous evaluation study of the "intensive neurophysiology education" carried out by Moseley et al [27]. We put the significance level (alpha) to 5% with the probability of at least 80% to discover a difference between the two intervention groups. If the difference between mean changes in the two groups is at least 10% (approximately 2-3 points) with SD of 3, we will need approximately 50 patients in each group. Adjusting for the cluster design of 20 different clusters and loss to follow-up we end up with 150 patients in each group, total n = 300 patients, that is 75 patients in each block. It seems from this sufficient if each provider recruits 7 or 8 patients each in order to obtain 300 in total.

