## Discussion

We present the rationale and design for an RCT examining the effects of a specific cognitive based education model for management of sub-acute LBP in normal primary care settings. The primary outcome will be disability as measured by Roland-Morris Disability Questionnaire. The secondary outcomes include pain, return to work, patient satisfaction, quality-of-life, and cost utility. Data collection will take place at inclusion, at the end of the four-week treatment programme and at 12 months. The study period will go through 2009 and 2010 and the results will be available in 2012.

If the study succeeds in demonstrating a significant positive effect on any of the outcome measures, the potential gain is huge, not only for the LBP patients, but also for the societal costs and for the health care, because of the large number of patients and their disability.

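### The Data analysis section labels days to return to work as primary although it is a secondary outcome elsewhere, so its significance threshold is 0.05 or 0.01 depending on the section read

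*Protocol article*

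**What the plan says.** Three sections of the protocol article name the primary outcome as function or disability on the RMQ:

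- Outcome measures makes function, assessed by the RMQ, the primary outcome, and places return to work in the list of secondary outcomes.
- Sample size: "The primary outcome of the study is patient-reported function as measured on a continuous measure".
- Discussion: "The primary outcome will be disability as measured by Roland-Morris Disability Questionnaire. The secondary outcomes include pain, return to work".

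The Abstract and the end of Background give aims and do not name an instrument. The order is the same: increased function is the primary aim and earlier return to work is a secondary aim.

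Data analysis differs: "For the primary outcome of days to return to work a survival curves analysis with a log-rank statistic will be used", followed by Cox regression for the same outcome. The other measures are given a mixed model with group as a fixed factor. The RMQ is not mentioned in that section. The section also ties the threshold to the label: 0.05 for primary outcomes (in the plural) and, in its own words, "For the secondary outcomes a p value of < 0.01 will be considered statistically significant".

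**The concern.** In many protocols a misplaced label in the analysis section would be cosmetic. Here the label selects the significance threshold, so the same return-to-work result has two decision rules. The article has no sentence saying which section governs, and no division or ordering of alpha that would apply if two primary outcomes were meant.

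Two things are at stake. The first is the standard of evidence for return to work, which is 0.05 under Data analysis and 0.01 under Outcome measures and Discussion. The second is the identity of the primary result. A reader who combines the label in Data analysis with the label elsewhere has two outcomes that can each claim 0.05, and only one of them has a sample size behind it. Data analysis also says that the number of analyses will be restricted to limit type I errors, and an ambiguous primary label works against that aim.

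**Working it through.** **1. The sections side by side**

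| Section | RMQ function | Return to work |
|---|---|---|
| Abstract, Background (aims) | function is the primary aim; RMQ not named | secondary aim |
| Outcome measures | primary | secondary |
| Data analysis | not named; falls under the remaining measures | primary (days to return) |
| Sample size | primary | not mentioned |
| Discussion | primary | secondary |

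Data analysis is the only section that calls return to work primary.

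**2. Consequence for one result**

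Inputs, both from Data analysis: 0.05 for primary and 0.01 for secondary outcomes. Ratio: 0.05 / 0.01 = 5. Take a log-rank p of 0.03 as an illustration. With the primary label, 0.03 < 0.05 and the result is significant. With the secondary label, 0.03 > 0.01 and it is not. The same holds for every p from 0.01 up to 0.05. This step needs no assumption.

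**3. Error rates under each reading**

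Let a₁ and a₂ be the levels for the RMQ and for return to work. If the tests are independent, P(at least one false positive) = 1 − (1 − a₁)(1 − a₂).

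- RMQ the only primary (0.05), return to work secondary (0.01): 1 − 0.95 × 0.99 = 0.0595. The error rate for the primary is 0.05.
- Return to work the only primary (0.05), RMQ at 0.01: again 0.0595, and again 0.05 for the primary.
- Both primary at 0.05: 1 − 0.95 × 0.95 = 0.0975. Under any dependence the bound is 0.05 + 0.05 = 0.10.

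The article gives no correlation between the two test statistics, so a range is assumed. For two-sided tests with bivariate normal statistics, the chance is 1 − P(|Z₁| < z₁, |Z₂| < z₂), where z₁ and z₂ are the two-sided critical values:

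| Assumed correlation | Both at 0.05 | RMQ 0.05, return to work 0.01 |
|---|---|---|
| 0 | 0.0975 | 0.0595 |
| 0.3 | 0.0951 | 0.0587 |
| 0.5 | 0.0907 | 0.0572 |
| 0.7 | 0.0835 | 0.0547 |
| 0.9 | 0.0704 | 0.0510 |

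These figures cover the two outcomes only. They leave out the other secondary outcomes and any effect of clustering on the test statistics.

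**4. What the sample size supports**

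Inputs from Sample size: difference 2 points, SD 3, alpha 5% (two-sided assumed), power at least 80%, stated result about 50 per group before inflation for clustering and loss to follow-up.

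n = 2 × (z for alpha + z for power)² × SD² / difference²

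- 80% power: 2 × (1.960 + 0.842)² × 9 / 4 ≈ 35.3, so 36 per group.
- 90% power: 2 × (1.960 + 1.282)² × 9 / 4 ≈ 47.3, so 48 per group.
- Power with 50 per group: 2 / (3 × √(2/50)) = 3.33; 3.33 − 1.96 = 1.37, which gives 91.5%.

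The stated 50 is not what 80% power requires. It fits about 90%, and since the text says at least 80% and approximately 50, it is conservative and not an error on this point. What matters here is that every input concerns the RMQ. The section gives no event rate or hazard ratio, so it offers no power basis for return to work as a primary outcome.

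**The case against.** The strongest reply is that the intention is plain. Three sections name the RMQ as primary, the trial is sized on it, and one phrase in Data analysis is out of line. On this view it is a slip, and calling the RMQ one of the remaining measures may only separate time-to-event methods from mixed-model methods. Most of this stands: the weight of the text favours the RMQ, which is why the correction is easy. But the slip sits in the section an analyst follows, and there the label fixes the threshold. Knowing the likely intention does not remove the conflicting rule.

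A reader might also infer more than the article supports:

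- *That the trial's 5% error rate fails.* The 5% in Sample size belongs to the RMQ comparison, and no familywise rate is stated. The RMQ test keeps its own 5% even if return to work is also tested at 0.05.
- *That 9.8% is the plan's error rate.* It arises only if both outcomes are taken as primary and are independent. The plural in the threshold sentence allows that reading but does not establish it. If either one alone is primary, the pair is tested at 0.05 and 0.01.
- *That the Discussion makes success on any outcome a trial success.* The sentence "If the study succeeds in demonstrating a significant positive effect on any of the outcome measures, the potential gain is huge" is a closing remark about potential benefit. It sets no decision rule and leaves the 0.01 threshold untouched.
- *That the sponsor means to choose the primary after seeing results.* Nothing in the article suggests this. A blinded statistician is specified and a switch would be visible against the text, although blinding does not settle which label applies.

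**Conclusion.** The point holds as a contradiction in the decision rule, and Data analysis is wrong as written. It gives days to return to work the primary label and hence 0.05, whereas Outcome measures and Discussion make return to work secondary and hence subject to 0.01. Nothing else in the article resolves this.

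The certain part of the effect is the fivefold difference in the return-to-work threshold. The conditional part is a chance of at least one false-positive primary of about 9.8% (9.5% to 7.0% for correlations of 0.3 to 0.9) against 5% for a single primary. That part assumes that both outcomes are treated as primary, two-sided tests and bivariate normal statistics, and the correlations are assumed, not documented. The case rests on Outcome measures, Sample size and Discussion. The aims agree with them but name neither the RMQ nor a primary outcome, so they are supporting evidence only.

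**What to change.** In Data analysis, change primary to secondary in the sentence on days to return to work, and state that it is tested at p < 0.01. In the same section, name the RMQ as the single primary outcome, analysed by the mixed model at p < 0.05, and put the threshold for the primary outcome in the singular.

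If two primary outcomes are really intended, Outcome measures, Sample size and Discussion must be changed, together with the aims in the Abstract and Background, and alpha must be split or ordered between the two.

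The first option costs a few words and changes no data collection, analysis method or sample size. It should be settled before any comparison between the groups is seen. The Discussion sentence on potential gain need not change to resolve this conflict.

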**Methods/Design:**

Cluster randomised controlled trial with 20 general practitioners and 20 physiotherapists in primary care as the unit of randomisation. Each practitioner will recruit up to 10 patients, aged 20 to 55 years, with non-specific sub-acute/chronic LBP of more than four weeks but less than 1 year's duration. Practitioners in the intervention arm will provide cognitive patient education intervention in up to four weekly sessions, each lasting 30 minutes. Practitioners in the control arm will provide normal treatment, but have to make four appointments for the patients. Patients, outcome assessors, and study statistician will be blinded to group allocation.

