## Methods/Design

### Design

This study is a stratified cluster randomised controlled trial taking place in primary care with family doctors (GP) and physiotherapists (PT) in Oslo and Akershus County in Norway. The design contains two arms in which 20 GPs and 20 PTs will be stratified into, and then randomised to either the intervention or the control provider group. Each cluster will contain the GPs/PTs and their included patients.

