### Recruitment of practitioners

An invitation to an information meeting regarding the project was sent out to all GPs and PTs working in the primary health care in Oslo and Akershus County in Norway in March 2008. After an information meeting, the practitioners were invited to participate in the study. A total of 20 GPs and 20 PTs were included and randomised.

Strategies to promote participation of practitioners into the trial included offering professional development points and financial compensation for the extra time spent on recruiting patients to the project, as well as treatment of included patients.

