### Randomisation and allocation procedure

GPs and PTs were randomly allocated to either the intervention or control group. A block randomisation procedure with stratification for type of health care provider (GP and PT) was carried out to ensure a similar number of participants in the four blocks (GP and PT intervention, GP and PT control). The randomisation procedure was carried out by computer-generated numbers that were placed in closed non-transparent envelopes. An independent person administrated this procedure. Patients and outcome assessors will be blinded regarding group allocation.

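### Return to work is assigned a log-rank test and Cox regression with no allowance for randomisation by provider, so in their standard form its p-values and confidence intervals would be too optimistic

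*Protocol article*

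**What the plan says.** The trial is clustered by design. The abstract calls it a "Cluster randomised controlled trial with 20 general practitioners and 20 physiotherapists in primary care as the unit of randomisation". The Design section defines the cluster: "Each cluster will contain the GPs/PTs and their included patients". Recruitment of practitioners reports that "A total of 20 GPs and 20 PTs were included and randomised", and the allocation section that "A block randomisation procedure with stratification for type of health care provider (GP and PT) was carried out".

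The Sample size section allows for this: "Adjusting for the cluster design of 20 different clusters and loss to follow-up we end up with 150 patients in each group". It expects that "each provider recruits 7 or 8 patients each in order to obtain 300 in total".

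For days to return to work, the Data analysis section states that "a survival curves analysis with a log-rank statistic will be used to assess differences between the groups", with Cox regression for the effect of treatment group on the hazard. It mentions no frailty, no robust variance and no cluster-adjusted test. The mixed model in the next sentence is for the remaining outcomes, so return to work lies outside it. The same section tests primary outcomes at 0.05 and secondary outcomes at 0.01.

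**The concern.** A standard log-rank test and a standard Cox model count each patient as an independent unit. Here the provider is the independent unit. Patients of one provider may resemble each other, and the article itself gives reasons to expect this: each provider recruits and treats their own patients, and control care is left to that provider's usual practice. With any positive correlation, the patient-level standard error is too small, the test rejects too often under no effect, and the hazard-ratio interval is too narrow.

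The plan is therefore inconsistent. It pays for clustering in the sample size, then names a test for one outcome that, as usually run, ignores it. The outcome matters: return to work is one of the two bases of the cost-effectiveness analysis, and the Discussion attaches a large potential gain to a significant effect on any outcome. A significant result from these tests could be dismissed as a unit-of-analysis error.

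**Working it through.** **The plan's own figures.** The article states no event count, hazard ratio or power for return to work, so there is no figure for this outcome to reproduce. The cluster size can be checked: 300 patients / 40 providers = 7.5, which agrees with the planned 7 or 8. The base sample size for the Roland Morris score (difference 2, SD 3, two-sided 5%, 80% power) comes out at 36 per group against the stated 50 or so. With 50 per group the power is 91.5%, which is compatible with at least 80%. This does not bear on the present point.

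**Inputs.**
- 40 clusters, about 20 per arm (Recruitment of practitioners; Randomisation and allocation procedure).
- Mean cluster size m = 7.5 if all patients contribute (Sample size).
- m = 3.75 if half contribute. This is an assumption: the eligibility criteria do not require sick leave, so patients at work at entry may add nothing to a time-to-return analysis.
- Nominal levels 0.05 and 0.01 (Data analysis), taken as two-sided because the article does not say.
- ICC not given; assumed 0.02, 0.05 and 0.10.

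**Formulas.** Design effect DE = 1 + (m − 1) × ICC. True size of an unadjusted test = 2 × [1 − Φ(z/√DE)], with z = 1.960 or 2.576. The correct interval is √DE times as wide as the unadjusted one.

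**Example.** For m = 7.5 and ICC 0.05, DE = 1 + 6.5 × 0.05 = 1.325 and √DE = 1.151. Then 1.960/1.151 = 1.703, which gives a true size of 0.089, and 2.576/1.151 = 2.238, which gives 0.025.

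| m | ICC | DE | √DE | True size, nominal 5% | True size, nominal 1% |
|---|---|---|---|---|---|
| 7.5 | 0.02 | 1.130 | 1.06 | 6.5% | 1.5% |
| 7.5 | 0.05 | 1.325 | 1.15 | 8.9% | 2.5% |
| 7.5 | 0.10 | 1.650 | 1.28 | 12.7% | 4.5% |
| 3.75 | 0.02 | 1.055 | 1.03 | 5.6% | 1.2% |
| 3.75 | 0.05 | 1.138 | 1.07 | 6.6% | 1.6% |
| 3.75 | 0.10 | 1.275 | 1.13 | 8.3% | 2.3% |

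At ICC 0.01 and m = 7.5, the nominal 5% test has a size of 5.8%, so the problem is then small.

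**Check by simulation.** An unadjusted log-rank test was run under no treatment effect, with 40 clusters of about 7.5, a gamma frailty shared within provider, an assumed hazard of 0.012 per day, censoring at 365 days and 8,000 runs per setting. For frailty variances of 0.05, 0.10 and 0.20, it rejected at nominal 5% in 9.0%, 12.2% and 18.0% of runs with all patients contributing, and in 6.8%, 9.2% and 12.1% with half. With no frailty the rates were 5.8% and 5.1%, so the all-patients figures should be read against 5.8% rather than exactly 5%. Frailty variance is not the same scale as the ICC, but direction and order of size agree with the table.

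**The case against.** The strongest reply is that much of this is silence. The authors call the trial cluster randomised and adjust its size, so they know of the issue. A Cox model with a provider frailty or clustered variance is still Cox regression, and the article excludes neither. Variance estimation is commonly left to a statistical analysis plan, which is not at hand. This has force for the Cox wording. It has less for the log-rank test, which is named as the test of group differences and is unadjusted in its standard form. Nor does it explain why return to work is kept apart from the one model class named that could carry a provider effect. A later plan could repair this only by adding to or departing from the published text.

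Two further objections limit size and grade, and both stand. Not all patients need contribute to return to work, so figures based on m = 7.5 may overstate the inflation. The abstract, Background, Outcome measures and Discussion all list return to work as secondary; only one phrase in Data analysis calls it primary. At the secondary threshold of 0.01, the true error in the table stays below 5%.

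A reader might extend the point to the odds ratios, given "in categories with odds ratio for categorical data". That sentence is about how differences will be presented. It names no test, and the other outcomes are assigned to a mixed model. A reader might also infer that the mixed model ignores provider because only group is named. Group is named as the fixed part; a mixed model has a random part by definition, and leaving it unnamed in a condensed article is not a stated error.

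**Conclusion.** The point holds for return to work alone. As written, the named methods are anti-conservative for any positive within-provider correlation. The direction is certain on that condition; the size is not, because the ICC and the share of patients contributing are both assumed. Over ICC 0.02 to 0.10, true size runs from 5.6% to 12.7% at nominal 5% and from 1.2% to 4.5% at nominal 1%. Intervals would need widening by a factor of 1.03 to 1.28.

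Two stronger readings are not supported. One takes the step from 50 to 150 per group as the sponsor's own design effect: 150/50 = 3, or 3 × 0.7 = 2.1 with an assumed 30% loss, for which an unadjusted 5% test has a size near 18%. That allowance was made for the disability score, and its split between clustering and loss is not given, so it says nothing firm about return to work. The other takes the trial's main conclusion to be at risk. The disability score is the primary outcome in the Outcome measures and Sample size sections, and its analysis does not use the log-rank or Cox methods. The article also does not say that the log-rank p-value or the Cox interval enters the cost-effectiveness analysis. This should be fixed, but it does not undermine the trial.

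**What to change.** Reword the return-to-work paragraph in Data analysis so that inference comes from a Cox model that accounts for provider, through either variance clustered on provider or a shared provider frailty, stratified by provider type (GP or PT) to match the randomisation. Name one of the two in advance. If robust variance is chosen, a small-sample correction is sensible with about 40 clusters. Either replace the log-rank test with a cluster-adjusted version or keep the survival curves as description without a p-value.

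The paragraph should also state which patients enter this analysis, since that sets the effective cluster size.

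No new data are needed: patients are enrolled through their provider, so the provider identifier should already be held. The cost is a change of wording, somewhat wider intervals (by the √DE factors above) and some loss of nominal significance.

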### Recruitment of patients and eligibility criteria

Each participating GP and PT in both intervention and control groups will consecutively ask eligible patients to participate in the study. The study is thus taking place in a normal clinical setting. The inclusion criteria are:

• Men and women aged 20 - 55

• Unspecific LBP

• Duration from 4 weeks up to 1 year since onset of actual pain episode

• Signed informed consent

• A score ≥ 4 on the Roland Morris Disability Questionnaire

The following criteria excluded patients from participation:

• Provider's uncertainty of diagnosis; possible nerve root pain or severe pathology

• Signs of any 'red flags'

• Particular interest in or demand for a specific treatment

Consequently, all patients visiting his or her provider because of back pain will be assessed according to these inclusion and exclusion criteria. If the patient is found eligible, he or she will be asked to participate. Those who agree to participate will sign a consent form and receive the questionnaires described later. The patients may either answer the questionnaires immediately in the provider's waiting room, or at home. In both cases the forms will be sent in a stamped and addressed envelope before the first session of the trial. The provider will inform the study management by an enrolment fax and arrange for the first session within a week of inclusion. Those who do not want to participate in the study or fail to satisfy the criteria will be registered by initials, year of birth, score on the Roland Morris Disability Questionnaire and the reason for not participating. All the procedures are identical for both intervention and control groups.

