### Data collection

Patients will initially be asked by the provider to answer the questionnaires in the waiting room immediately after signed consent. At baseline the patients will fill in a registration form and a baseline questionnaire regarding sociodemographics (age, gender, marital status, education, and work status), other diseases, use of medicines, a standardised screening questionnaire on psychosocial risk factors - the Örebro Musculoskeletal Pain Questionnaire [29,30] and the baseline measures of the outcomes. In addition, three standardised questionnaires assessing beliefs about pain, the Pain Catastrophizing Scale [31], the brief version of the Illness Perception Questionnaire [32,33], and beliefs about LBP [20] will be included. The two first questionnaires will be translated into Norwegian and tested for psychometric properties before start of the main study.

During the first four weeks, all the patients will fill in a weekly report regarding work status and pain rating. The patients will be contacted again after 4-5 weeks, and after 3, 6, and 12 months after inclusion. At 4-5 weeks, 3 and 6 months, the patients will be contacted by telephone for the registration of work status and pain rating, and at 4-5 weeks and 12 months follow-up the patients will also fill in a postal comprehensive questionnaire including outcome measures and questions about possible co-intervention.

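### The mixed model for the RMQ names only group as a fixed factor and leaves other covariates to unspecified confounder testing; baseline RMQ and the GP/PT stratum should be pre-specified

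*Protocol article*

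**What the plan says.** The Sample size section makes the RMQ primary: "The primary outcome of the study is patient-reported function as measured on a continuous measure". The Data analysis section gives return to work its own survival methods and then says: "A mixed model with group as a fixed factor will be used for the other outcome measures". The RMQ falls under that sentence. Group is the only fixed factor named. On other covariates the section says only: "We will also test for potential confounding factors in these models". None is named.

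Two variables known before the analysis are not mentioned there:

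- **Baseline RMQ.** The Data collection section lists, among what patients complete at inclusion, "the baseline measures of the outcomes". The RMQ is also scored for eligibility: "A score ≥ 4 on the Roland Morris Disability Questionnaire".
- **Provider type.** The Randomisation and allocation procedure section says: "A block randomisation procedure with stratification for type of health care provider (GP and PT) was carried out".

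The Sample size section frames the target as a difference between mean changes (2 to 3 points, SD 3). The Data analysis section does not say whether the modelled RMQ is a change or a follow-up score.

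**The concern.** Baseline RMQ would be expected to predict follow-up RMQ, and provider type is part of the design. Whether they enter the primary model should be settled in advance. The stated rule leaves them, at best, to a test during the analysis. That makes the primary estimate depend on a data-driven choice, and it fits poorly with the same section's aim of limiting the number of analyses to control false positives.

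Three things are at stake:

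- **Precision.** Without baseline, predictable patient variation stays in the residual. Without the stratum, any GP-PT difference is counted as between-provider variance. Stratification has already balanced that difference across arms, so the reported standard error would be larger than it need be.
- **Imbalance.** Providers were randomised first and then recruit their own patients, and those in the intervention arm have been trained and know their arm. Baseline adjustment gives partial protection if the arms recruit patients of different severity, or differ by chance.
- **Discretion.** With no named covariates, more than one primary model is consistent with the text.

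**Working it through.** **The plan's own figure.** The article gives no figure for adjustment. Its effect (2 points), SD (3), two-sided 5% alpha (sidedness assumed) and 80% power give 2 × (1.960 + 0.842)² × 9/4 ≈ 35.3, so 36 per group against its approximately 50. With 50 per group power is 91.5%. The difference is conservative and does not bear on this point. Only the 2 points, the SD of 3, the 150 patients and 20 providers per arm (7.5 patients each), and the equal GP/PT split are used below.

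**Assumptions, because the documents give no values.** Baseline/follow-up correlation ρ of 0.3 to 0.7; ICC 0.05; GP-PT difference D of 0.5 to 2 points; 20% loss to follow-up where stated.

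**Step 1: baseline adjustment.** With equal SDs at both times, the residual variance relative to an unadjusted follow-up score is 1 − ρ². Relative to a change score it is (1 − ρ²)/[2(1 − ρ)] = (1 + ρ)/2.

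| ρ | against follow-up | against change | 150 adjusted patients could be replaced by (follow-up / change) |
|---|---|---|---|
| 0.3 | 0.91 (−9%) | 0.65 (−35%) | 137 / 98 |
| 0.5 | 0.75 (−25%) | 0.75 (−25%) | 113 / 113 |
| 0.7 | 0.51 (−49%) | 0.85 (−15%) | 77 / 128 |

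The last column is the number of patients per arm who, with adjustment, give the precision of 150 without it (150 × ratio, rounded up). Neither ratio exceeds 1, so adjustment is at least as precise whichever score was intended.

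**Step 2: stratum.** Total variance is 9, so at ICC 0.05 the between-provider part is 0.45 and the within-provider part 8.55. The variance of a provider mean is 0.45 + 8.55/7.5 = 1.59. With half the providers in each stratum, leaving the stratum out adds D²/4.

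- D = 0.5: √(1.6525/1.59) = 1.02
- D = 1: √(1.84/1.59) = 1.08
- D = 2: √(2.59/1.59) = 1.28

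With 6 analysed patients per provider (20% loss), and a small-sample factor of 40/38 on D²/4, D = 1 gives a standard error of 0.462 against 0.433, about 7% wider.

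**Step 3: interval and power.** With 120 analysed per arm, 6 per provider, the design effect is 1 + 5 × 0.05 = 1.25.

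- Unadjusted: SE = 3 × √(2 × 1.25/120) = 0.433; half-width 1.96 × 0.433 = 0.85; power for 2 points = Φ(2/0.433 − 1.96) = 99.6%.
- Baseline-adjusted, ρ = 0.5: SE = 0.433 × √0.75 = 0.375; half-width about 0.73; power 99.96%.

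This takes the ICC as unchanged by adjustment. At ρ = 0.5 the result is the same whether the SD of 3 refers to a follow-up score or a change, because both ratios in Step 1 are 0.75.

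**Step 4: chance imbalance in baseline RMQ.** Taking SD 3 and ICC 0.05 for baseline as well, the SE of the difference between arms is √(2 × 1.59/20) = 0.40, a 95% range of about ±0.8 points against a 2-point target. An imbalance above 1 point has a probability of about 1%.

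**The case against.** **The text is silent rather than exclusive.** Naming group as a fixed factor does not make it the only one, and a condensed article may leave a covariate list to a plan that is not shown. A reader might infer that the model excludes baseline and stratum; the article does not say so. What remains is that the article does state a covariate policy, unspecified testing, and for these two variables that is the weaker rule.

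**Imbalance is not ignored.** A reader might infer that imbalance is likely and would go uncorrected. The confounder sentence contradicts the second part, since it could bring both variables in. The first part is not shown: large chance imbalance is improbable (Step 4), and the documents give no evidence of differential recruitment, only a design in which it can occur.

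**Baseline may already be used.** If change is modelled, as the sample size wording suggests, baseline enters by subtraction. That is fair, and it is why Step 1 gives both comparisons. Adjustment still gains against change.

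**The stratum effect can be overstated.** No passage says that GP and PT patients differ in RMQ, so it cannot be stated as fact that the standard error is too large. The 28% widening needs a gap as large as the target effect. If the ICC of 0.05 covers all providers, including the GP-PT gap, then D²/4 ≤ 0.45 and D cannot exceed about 1.3. Baseline RMQ would also absorb part of any gap, so the two gains do not add. Omitting the stratum is conservative and does not inflate type I error.

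**Conclusion.** The point holds as a matter of pre-specification and precision. The article names one fixed factor for the primary RMQ model and leaves the rest to unnamed confounders, although baseline RMQ and provider type are known and available. Baseline adjustment lowers variance by 9 to 49% against a follow-up score, or 35 to 15% against a change score, as ρ goes from 0.3 to 0.7. The stratum matters only as far as GP and PT patients differ: about 8% on interval width at a 1-point gap, about 2% at half a point.

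A reader might conclude that the trial is underpowered or its test invalid. The documents support neither: on the article's own effect and SD, power exceeds 99% at ICC 0.05 with or without baseline adjustment. The benefit is a narrower interval, protection against chance or recruitment imbalance, and less discretion over the primary model. The correlation, ICC, GP-PT gap and loss rate are all assumptions, so the sizes are indicative. That adjustment does not lose against either unadjusted score follows from the formulas in Step 1.

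**What to change.** State the primary model as follow-up RMQ on group, baseline RMQ and provider type (GP/PT) as pre-specified fixed effects, with provider as a random intercept. Say that these two terms are included whatever any test shows, so that confounder testing no longer decides on them. Use the same structure, with the matching baseline value, for pain, EQ-5D and PGI.

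The cost is one or two sentences in the analysis plan. Baseline values and provider type are already recorded, so no new data and no change to recruitment or follow-up are needed.
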